### Data collection and management

Research assistants blinded to the allocation will be trained in data collection. Participants will be observed and surveyed using questionnaires throughout the study period. The medium-term and long-term effects of the intervention were evaluated by repeated measurements using the same standardized procedures before, 12 months, and 24 months after the intervention.

All collected data will be kept strictly confidential and properly preserved, and all relevant regulations will be observed. Each participant is identified by a unique code instead of a name. All research data can only be obtained by designated research team members before analysis. These data were initially registered on paper questionnaires by investigators and then entered into electronic data through Epidata 3.1 software after the investigation. Electronic data is stored on password-protected computers, and paper questionnaires are stored in locked filing cabinets. When collecting data, the project manager will check all data for omissions or errors and record any problems with the data. Before analyzing the data, the lead researcher (PI) and statistician will review it again. Information collected from the study will be preserved until the project is completed. From the date when the study results are published, they will be preserved for at least 5 years.

### Statistical methods

#### Primary and secondary outcomes

The primary purpose of the analysis was to investigate the effects of multicomponent interventions (targeted promotion campaigns, providing free cards and chess leisure activities tools) on objectively measured cognitive function and neuropsychiatric state, compared with the usual practice at 24-month follow-up.

The primary outcome analysis is powered to detect a significant difference in cognitive function and neuropsychiatric status in the older people over 60 years at the end of a 24-month follow-up period. Linear multilevel models will be used to analyze the cognitive function and other neuropsychiatric indicators as outcome variables. Levels indicate the clustering of residents within villages. We take the randomly divided classification variables as independent variables (the intervention group will be compared with the control group), and age, family history of dementia, baseline value, smoking, drinking, and sleep quality as confounding factors. In these linear multilevel models, village clusters will be included as a random effect to simulate the heterogeneity of residents in villages. The model will use restricted maximum likelihood estimation.

After the survey, the differences in baseline characteristics between participants who completed the whole survey and those who dropped out of the study will be compared. Multiple interpolation and sensitivity analyses of missing data are carried out to evaluate the influence of missing data on the obtained results. The effect size of the protocol will be determined by the subjects who participated in the study and completed follow-up. Secondary outcomes measured at other time points will be analyzed using similar methods. In addition, we will use repeated measurement variance analysis to evaluate the changes in the main outcome indicators of each protocol at each time point. Subgroup analyses are planned for baseline characteristics that might affect the primary outcomes.

The p values of all tests are two-sided and the test level α is 0.05. Estimates will also be reported with a 95% confidence interval.

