### Cluster and participant recruitment

The study areas are selected by an expert consultation method. First, we selected Helan County of Yinchuan, Litong District of Wuzhong City, Qingtongxia City, and Shapotou District of Zhongwei with high-quality public health work to carry out this study. In the second stage of sampling, taking villages as the basic unit, two villages are randomly selected from the eligible villages in the above four project research areas, and the selected villages are matched (1:1) as control villages and intervention villages respectively. The matching principle is based on the county to which the village belongs.

The selected villages need to meet the following conditions:The population aged 60 is ≥ 100.Residents have fewer daily leisure activitiesVillage cadres/village doctors are serious and responsible.

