### Primary outcomes

#### Cognitive function

The Mini-Mental State Examination (MMSE) [34, 35] and Montreal Cognitive Assessment (MoCA) [36] are simple, low cost and noninvasive methods of screening MCI due to Alzheimer’s disease (AD). Numerous studies stated that MMSE and MoCA accuracy in detecting MCI due to AD was inconsistent when selecting different reference standards as the “gold standard. In addition, they selected different cutoff values for positivity. To date, there is still no consensus on which neuropsychological test performs better at detecting MCI due to AD. In addition, international criteria are more suitable as a reference standard for evaluating diagnostic tools' accuracy. Studies have shown that the combined use of MMSE and MoCA scales for cognitive impairment diagnosis is more accurate than MMSE or MoCA scales alone. Therefore, we use MMSE and MoCA together to assess cognitive function. The ability to perform activities of daily living (ADL) is a vital part of the assessment in neurologic patients. An ADL scale was used to evaluate subjects' functional status in real life. It consists of two parts: the Physical Self-Maintenance Scale (PSMS) and Instrumental Activities of Daily Living (IADL).

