#### Demographic

During their baseline visit, we obtained the following covariates from face-to-face interviews: age, sex, education level, living conditions (living alone or with others), family relations, and monthly income. In addition, participants will report previous illnesses (such as hypertension and diabetes) and a family history of dementia. At each follow-up, participants will be asked if there has been any change in these areas. If yes, it will be revised and the latest follow-up information will be used.

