### Sample size

PASS 15.0 software calculated the sample size. Power calculation indicated that with a sample size of 4 clusters in each group and 100 observed objects in each cluster, this study would have 88% power to detect the change in cognitive function with a mean of 1, a standard deviation of 2, and a two-tailed significance level of 5%. As a result of the correlation coefficients being set to 0.050 within clusters, and the coefficients of variation being set to 0.650, four clusters in each group, resulting in a total of 800 people to be recruited. The power of RCT over 80% is considered acceptable [41], so the sample size calculated in this study will be eligible.

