### Assignment of interventions: allocation

#### Sequence generation

In this cluster randomized controlled trial (RCT), 8 villages will be recruited. A village is a cluster. To reduce contamination risk, clusters will be randomized at the village level. Using a computer-generated list, statisticians at Ningxia Medical University randomly assigned villages (clusters) to one of the two groups and stratified them according to the counties to which villages belong before allocation. The randomization will be performed using a computer-generated randomization table in Microsoft Excel.

Randomization will be carried out after the cluster completes the baseline measurement. These clusters will be recruited from Helan County, Litong District, Qingtongxia City, and Shapotou District in Ningxia, China. Our goal is to recruit 800 over-60 s in 8 clusters. Clusters will be randomly assigned to accept one of the following conditions: (1) intervention groups that distribute leisure activities tools (chess and cards) free of charge and promote them, or (2) control groups (routine).

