## Discussion

With the increase in age, the probability of cognitive impairment in the older people is on the rise [42, 43]. More and more evidence shows that participating in cards and chess leisure activities is beneficial to the cognitive and psychiatric state of the older people [18, 19]. Although previous cross-sectional or cohort studies have shown beneficial prospects for leisure activities [44, 45], the quality of the study design is low. Many previous studies have not fully considered baseline cognitive state and other confounding factors, both of which may lead to bias, and no effective cluster randomized controlled trials are underway. Advantages of this study include robust randomized controlled trial design, randomization at the cluster level to reduce contamination, large population, including medium-term and long-term follow-up measures, and strict objective scale measurement as the main results. In addition, the uniqueness of this study is that it will clarify the influence of the frequency and duration of participation in chess and cards activities on cognitive function. Inevitable limitations of this study include: First, due to the nature of this study, participants cannot turn a blind eye to the interventions they receive, and if researchers interact with subjects, they cannot keep blind to researchers, which may lead to information bias. Second, basic information, the duration and frequency of leisure activities are reported by the subjects themselves, which may lead to recall bias. Nevertheless, the present study will fill gaps in the literature. This study will help to build an evidence base around the effectiveness of interventions to reduce cognitive impairment in the older people, and provide valuable information for successful aging.

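### Education level is collected at baseline but left out of the primary cognitive model; adding it would be a free, modest gain in precision

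*Protocol article*

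**What the plan says.** Under Statistical methods (Primary and secondary outcomes), the protocol article plans linear multilevel models fitted by restricted maximum likelihood, with study arm as the independent variable and village as a random effect. The adjustment set is written out in full: "age, family history of dementia, baseline value, smoking, drinking, and sleep quality as confounding factors".

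The Demographic section lists the covariates taken at the baseline interview as "age, sex, education level, living conditions (living alone or with others), family relations, and monthly income". Of these six, only age reaches the model. No reason is given for leaving out the others.

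On the outcome, the Cognitive function section says: "Therefore, we use MMSE and MoCA together to assess cognitive function".

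On the design, Sequence generation says: "In this cluster randomized controlled trial (RCT), 8 villages will be recruited". Sample size assumes "4 clusters in each group and 100 observed objects in each cluster". Cluster and participant recruitment says "the selected villages are matched (1:1) as control villages and intervention villages respectively", with county as the matching criterion, and Sequence generation says that the statisticians "stratified them according to the counties to which villages belong before allocation". No other balancing factor is named.

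Subgroup analyses by baseline characteristics are also planned, but they do not adjust the primary estimate.

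**The concern.** Schooling is a plausible predictor of scores on both cognitive tests. It is already being collected, yet smoking, drinking and sleep quality are in the model and it is not. With four villages per arm, mean schooling could differ noticeably between arms by chance, and county stratification does nothing about differences between the two villages of one county. The baseline score is a single imperfect measurement, so adjusting for it need not remove all of schooling's influence on the 24-month score. What remains adds noise to the arm comparison and can move the one estimate the trial will report. Precision matters in a trial with so few clusters.

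**Working it through.** **Inputs from the protocol (Sample size).** Design difference 1 point, SD 2, intracluster correlation (ICC) 0.05, 4 villages of 100 per arm. The protocol gives no figure for schooling: no distribution, no schooling ICC, no relation to the scores and no correlation between baseline and follow-up scores. Every schooling input below is therefore an assumption with a range.

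**Step 1: yardstick from the plan's own inputs.**
- Design effect = 1 + 99 × 0.05 = 5.95.
- Variance of the arm difference = 2 × 4 × 5.95 / 400 = 0.119, so the standard error is 0.345 points.
- Between-village variance = 0.05 × 4 = 0.20.

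With a normal approximation these inputs give about 83% two-sided power (80% allowing for the stated coefficient of variation of 0.65), not the stated 88%. That is a separate matter, and nothing below depends on it.

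**Step 2: chance imbalance in schooling.** In units of the schooling SD, the variance of the arm difference is (2/4) × [ICC + (1 − ICC)/100].

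| Assumed schooling ICC | SD of arm difference | P(difference > 0.25 SD) |
|---|---|---|
| 0.02 | 0.12 | 4% |
| 0.05 | 0.17 | 15% |
| 0.10 | 0.23 | 28% |
| 0.20 | 0.32 | 44% |

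The ICC should be read as within county. Each county supplies one village per arm, so differences between counties cancel.

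**Step 3: what survives adjustment for the baseline score, by two routes.**
- *In years of schooling.* SD of the shift = √(2/4) × within-county village SD × slope × (1 − reliability). Central case: village SD 1 year, 0.4 points per year, reliability 0.7 to 0.8. Then 0.707 × 1 × 0.4 × 0.2 = 0.057 and 0.707 × 1 × 0.4 × 0.3 = 0.085 points.
- *In SD units.* Shift = imbalance × schooling-score correlation × (1 − baseline-to-follow-up correlation) × 2. With imbalance 0.1 to 0.5 SD, schooling-score correlation 0.3 to 0.5 and baseline-to-follow-up correlation 0.5 to 0.8, the shift runs from 0.1 × 0.3 × 0.2 × 2 = 0.012 to 0.5 × 0.5 × 0.5 × 2 = 0.25 points. Without baseline adjustment it would be 0.06 to 0.50, so the planned baseline term removes 50% to 80%. These figures double if the score SD is 4.

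**Step 4: simulation with no true effect.** Twelve scenarios of 3,000 runs each, 8 villages of 100, schooling ICC 0.02, 0.10 or 0.20, schooling-score correlation 0.3 or 0.5, baseline-to-follow-up correlation 0.5 or 0.7, tested on village means with 6 degrees of freedom.

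| | Baseline score only | Baseline score + education |
|---|---|---|
| Type I error | 4.5-5.8% | 4.1-5.8% |
| Mean estimate | −0.007 to 0.005 | −0.009 to 0.006 |
| SD of estimate | 0.24-0.33 | 0.24-0.30 |

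The largest single gain (ICC 0.20, both correlations 0.5) was from 0.331 to 0.281, a 15% reduction. With ICC 0.02, schooling-score correlation 0.3 and baseline-to-follow-up correlation 0.7, the SD went only from 0.247 to 0.246.

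**Step 5: central case against the yardstick.** 0.057² / 0.119 = 2.7% and 0.085² / 0.119 = 6.1% of the planned variance. Removing that share shortens the standard error by about 1% to 3%, since 1 − √(1 − 0.027) = 0.014 and 1 − √(1 − 0.061) = 0.031.

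**The case against.** The strongest reply is that the analysis is sound as written. Arms are allocated at random, so a schooling imbalance averages zero. The village random effect carries what is left into the standard error, and the baseline outcome is already in the model. The simulation agrees on both validity and size: no bias, type I error near 5% either way, and often a small gain. This stands, and it limits the point to precision.

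It is also true that the protocol never says MMSE or MoCA depends on schooling. That premise is an assumption here.

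Four stronger readings are tempting, and the documents do not support them.
- *A schooling imbalance could pass as an intervention effect.* It can shift one realised estimate, but in an analysis that respects the village as the unit it does not raise the false-positive rate.
- *The leftover shift could reach a third of the target.* An SD of 0.34 follows from village SD 2 years, slope 0.8 and reliability 0.7 (0.707 × 2 × 0.8 × 0.3). Those inputs imply a leftover village variance of (2 × 0.8 × 0.3)² = 0.23, which exceeds the whole between-village variance of 0.20 implied by the sample size inputs.
- *The protocol breaks its own standard.* The Discussion says "Many previous studies have not fully considered baseline cognitive state and other confounding factors", but this concerns cross-sectional and cohort studies, where confounding is systematic. The first item it names, baseline cognitive state, is adjusted for here.
- *Sex is missing for the same reason.* Nothing in the argument or the calculations concerns sex. It is simply another collected covariate that is not used.

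What survives the reply is that education is already collected, that the written list leaves it out without a reason, and that including it did no material harm to precision in any scenario and helped in some.

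**Conclusion.** The omission is real and worth correcting, but it is a modest inefficiency. Under central assumptions the leftover schooling shift has an SD of about 0.06 to 0.09 points against the 1-point target, and removing it shortens the planned standard error by about 1% to 3%. Across the simulated range the SD of the estimate falls from 0.24-0.33 to 0.24-0.30 points.

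This rests on three assumptions that the protocol neither confirms nor denies: schooling predicts the scores, village mean schooling varies within county, and the baseline score captures only part of the relation. The gain would be larger if schooling strongly drove the rate of change over 24 months. The finding on type I error applies to a cluster-level test with 6 degrees of freedom, as simulated.

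**What to change.** In Statistical methods (Primary and secondary outcomes), add baseline education level to the fixed covariates of the linear multilevel models for MMSE and MoCA, as an individual-level term. Specify the baseline value, because the Demographic section lets follow-up reports replace earlier entries. Sex may be added in the same line as an optional covariate. If the sponsor prefers to leave education out, one sentence giving the reason would do.

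The change should be made and dated before outcome data are seen. Added later, once an imbalance is known, it would look data-driven.

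The cost is one line of text. No new data are needed. As an individual-level term, education uses none of the few between-village degrees of freedom.

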### Objectives

This study determined the long-term effectiveness of chess and cards leisure activities in improving cognitive and psychological status in older adults compared with those who did not pursue these activities.

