#### Primary objective

To investigate the effects of leisure activities using chess and cards entertainment tools on objectively measured cognitive function compared to usual practice at 24-month follow-up.

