#### Exclusion criteria

The participant may not enter the study if any of the following apply:In the study period, those who did not live in the village due to hospitalizations, traveling, or other reasons did not participate in the study.Aphasia, deafness, blindness, paraplegia, or other physical diseases and/or inability to communicate normally with others.Suffering from major diseases (severe heart, liver, kidney, lung, and metabolic diseases), nervous system diseases that can cause brain dysfunction, or those who have been at the end of their lives.Patients with severe mental disorders, depression, and dementia who have been diagnosed.Loss of daily living abilities.

Participants will receive concise information explanatory statements and an oral description of research details once they agree to participate. An explanation of the study's purpose, the procedure, the use of participant data, requirements of study participants during the 2-year activity, potential benefits and risks, how their information will be kept confidential, and contact information for any questions related to the project will be provided to participants both orally and in writing. Before any investigation is conducted, written consent will be obtained. At any time, participants will be informed that they can withdraw from the study and withdraw their consent. During the study, participants will be asked to maintain daily physical activity and eating habits. There will be no biological specimens collected in the present study.

As a reward for participating in the survey, participants will receive 20 RMB worth of paper towels and detergent. In medicine, the way to ensure participation in medical research through incentives is quite sensitive and controversial [31]. In the present study, although the compensation for the participants seems to be extremely low, the research conforms to the usual ethical standards of human subject research and will not bring additional risks to the subjects. We do not attract and supervise participants through compensation, they all participate in the research voluntarily.

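### As worded, the effect size comes from participants who completed follow-up, so the estimate depends on an event that happens after randomisation

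*Protocol article*

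**What the plan says.** Under Statistical methods (Primary and secondary outcomes), the protocol article sets out a linear multilevel model. It has randomised arm as the explanatory variable, village as a random effect, and adjustment for baseline value, age and other covariates. The next paragraph fixes whose data give the effect: "The effect size of the protocol will be determined by the subjects who participated in the study and completed follow-up".

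Two other statements there concern dropout. One is descriptive: "the differences in baseline characteristics between participants who completed the whole survey and those who dropped out of the study will be compared". The other covers imputation (printed as interpolation): "Multiple interpolation and sensitivity analyses of missing data are carried out to evaluate the influence of missing data on the obtained results".

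The Sequence generation section places allocation after baseline: "Randomization will be carried out after the cluster completes the baseline measurement". The primary time point is 24 months.

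The first exclusion criterion reads: "In the study period, those who did not live in the village due to hospitalizations, traveling, or other reasons did not participate in the study". It stands in a list introduced as conditions under which a person may not enter the study.

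**The concern.** Randomisation makes the arms comparable at allocation. It does not make those who remain two years later comparable. In people aged 60 and over, illness, hospital stays and withdrawal are plausibly linked to cognitive decline, which is the primary outcome.

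The design also gives reasons for loss to differ by arm. Participants know their allocation. Intervention villages receive games, monthly lectures and a trained local motivator, while control villages receive nothing extra. Blinded assessors do not remove this, because it is the participant who stays or leaves.

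If people who are declining leave one arm more often than the other, a completer comparison can create an effect or hide one. The exclusion criterion adds to this if it is applied to absences that begin after allocation.

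**Working it through.** The plan gives no loss rate and no bias figure, so there is nothing of its own to reproduce on this point. The check is first textual, then illustrative.

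**1. Order of events.** Consent comes before any measurement, baseline comes before randomisation, and follow-up is at 12 and 24 months. Completion is therefore known only after allocation, and selecting on it is selecting on a post-randomisation event.

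**2. Whether another sentence supplies an estimate in everyone randomised.**
- The imputation sentence describes a check on results already obtained. It does not say that the imputed analysis gives the reported effect.
- The comparison of completers with dropouts is limited to baseline characteristics. It can reveal selection but does not correct it.
- The levels of the primary model are residents within villages, with no level for repeated occasions, and other time points are to be analysed by similar methods. This suggests one model per time point. In that case the 12-month score of someone lost before 24 months would not inform the 24-month estimate.
- The repeated-measures analysis of variance, in its classical form, also drops incomplete cases.

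**3. How large the distortion could be.** Let p1 and p0 be the proportions lost in the intervention and control arms, and d the extra decline of those lost compared with those retained, the same in both arms. In each arm the full mean equals the completer mean minus p × d. The completer contrast therefore differs from the full contrast by

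shift = p1 × d − p0 × d = (p1 − p0) × d.

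The only inputs from the document are the 1-point target and the standard deviation of 2 in the Sample size section. The loss rates and d are assumptions.

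| Loss, intervention vs control | d (points) | Shift (points) | Share of 1-point target |
|---|---|---|---|
| 25% vs 15% | 2 | 0.25 × 2 − 0.15 × 2 = 0.2 | 20% |
| 30% vs 10% | 2 | 0.30 × 2 − 0.10 × 2 = 0.4 | 40% |
| equal loss, same mechanism | 2 | 0 | 0% |

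**4. A second mechanism as a cross-check.** Suppose dropout removes those lowest on a normally distributed trait that has correlation r with the outcome. With a fraction q lost, the completer mean rises by 2 × r × φ(z_q)/(1 − q), where φ is the standard normal density, z_q is the q-quantile of the standard normal distribution, and 2 is the standard deviation. For 20% versus 10% loss the shift is about 0.09 points at r = 0.3, 0.16 at r = 0.5 and 0.31 at r = 1.0. With 10% lost in both arms it is again 0.

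The sign depends on which arm loses more. Greater loss of decliners from the intervention arm favours the intervention; greater loss from the control arm works against it.

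**The case against.** Several points can fairly be made for the plan.

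- **The completer sentence does not use the word primary.** The model paragraph before it has no restriction to completers, and the sentence may be a translation of a supplementary per-protocol estimate. That is possible. However, the same paragraph goes on to use the word protocol in a way that points to the arms, and no sentence gives a primary estimate in all randomised participants. The plain reading is the completer reading, and on either reading the sentence needs correcting.
- **An article may leave analysis sets to a fuller document.** Agreed: the lack of an intention-to-treat label alone would be no finding. The point rests on a rule the article does state.
- **Imputation and baseline adjustment are planned.** Both help. Adjustment for baseline value and age would absorb part of any outcome-related loss, so only the extra decline left after adjustment matters. The illustrations above give no credit for this, and a d of 2 points is a full standard deviation, which is large.
- **The absence criterion is an entry criterion.** Its lead-in supports this. A reader might infer that residents who go into hospital later will be removed. The article does not say so, and its statistical section treats leavers as dropouts. Removal after allocation is only a possible reading of wording that refers to the whole study period.

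A reader might also infer from the general objective ("compared with those who did not pursue these activities") that the main contrast is players against non-players. The document does not support that. The primary objective is "objectively measured cognitive function compared to usual practice at 24-month follow-up", the control arm is defined by assigned villages, and the model compares the randomised groups. The general objective is loosely worded and selects nobody.

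**Conclusion.** The point stands in a limited form. As worded, the effect estimate is conditioned on completing follow-up and so is not fully protected by randomisation. The planned imputation softens this but is described as a check on the result, not as its source. The exclusion criterion is ambiguous about when it applies, and no more than that can be said.

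The document does not show that the result will be biased, or by how much. A reader might take 20% to 40% of the target effect as an estimate of the bias. It is not one: those figures rest wholly on assumed differential loss and an assumed extra decline, and loss that is equal in size and mechanism gives none. Nor would the change below remove all bias. A mixed model or standard imputation assumes data missing at random, and decline that no measured variable predicts would remain.

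**What to change.** 1. State that the primary estimate compares all consented participants according to the arm to which their village was randomised.
2. Obtain it from a mixed model that includes the 12- and 24-month scores, with village as a random effect and allowance for correlation between scores of the same person. Multiple imputation that respects the village structure is an alternative.
3. Make the completer analysis a sensitivity analysis. Add one for data not missing at random, since the primary model assumes missing at random.
4. Reword the absence criterion so that it applies only to status at or before baseline, and state that participants who are absent later stay in the analysis set.

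Because consent and baseline come before randomisation, the full set is already defined when villages are allocated, and scores are already collected at both follow-up times. The cost is a few sentences of wording, slightly more analysis work, and an open reliance on the missing-at-random assumption.

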#### Secondary objectives

To investigate the impact of intervention over the medium (assessed at 12 months) and long term (assessed at 24 months) on:Cognitive functionPsychosocial variables (anxiety, depression, and loneliness)Frequency and duration of chess and cards activitiesDaily activity functionKnowledge of cognitive impairment prevention

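### The supplementary repeated-measures ANOVA on the main outcomes names no village term, so its time-course p-values and intervals would be too optimistic if run in standard form

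*Protocol article*

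**What the plan says.** In the Protocol article, Statistical methods (Primary and secondary outcomes), the cognitive and neuropsychiatric outcomes are first assigned to linear multilevel models fitted by restricted maximum likelihood. The provision for clustering is tied to those models: "In these linear multilevel models, village clusters will be included as a random effect". Secondary outcomes at other time points are to be handled in a similar way.

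A further analysis is then added: "we will use repeated measurement variance analysis to evaluate the changes in the main outcome indicators of each protocol at each time point". No village factor, cluster-robust variance or village-level summary is attached to it, and it is not labelled descriptive. The section ends by making every test two-sided at 0.05 and promising 95% intervals.

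The design facts stand elsewhere in the article:
- Sequence generation: "clusters will be randomized at the village level".
- Sample size: the calculation concerns the change in cognitive function and uses "a sample size of 4 clusters in each group and 100 observed objects in each cluster", with "the correlation coefficients being set to 0.050 within clusters" and "the coefficients of variation being set to 0.650".
- Secondary objectives: "To investigate the impact of intervention over the medium (assessed at 12 months) and long term (assessed at 24 months"), with cognitive function first in the list that follows.

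**The concern.** In its standard form, a repeated-measures ANOVA models the correlation between visits of the same person. It does not model the correlation between residents of the same village. Here the village is the unit of randomisation and there are eight of them, so a standard ANOVA would treat about 800 residents as independent when the information on the arm difference is limited by the villages.

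Its p-values for the main outcomes would be reported beside those of the multilevel models, at the same significance level but with a different real error rate. Because an effect on cognition at 12 months is a stated objective, a small p-value from the ANOVA could be read as evidence of effect.

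The wording may instead mean change over time within each arm. The standard error is then too small for the same reason, and the result is not a randomised comparison.

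**Working it through.** **Inputs** (Protocol article, Sample size): 4 villages per arm, m = 100 residents per village (400 per arm), ICC = 0.05, coefficient of variation CV = 0.65, difference 1, SD 2, two-sided alpha 0.05, stated power 88%. The article does not say what the CV refers to; it is read here as the CV of cluster size.

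**1. The plan's own figure.** With SE = SD × √(2 × DE / 400), where DE is the design effect, power = Φ(1/SE − 1.96). This gives 82.6% at DE 5.95, 80.4% at DE 6.31 and 70.2% at DE 8.06. None matches 88%. A one-sided 5% test comes close (89.5% at DE 5.95, 87.9% at DE 6.31), but the article states a two-tailed level. This is a separate matter. The steps below use the ICC, cluster size, CV and SD, not the power.

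**2. Design effects at ICC 0.05.**
- Equal clusters: 1 + (100 − 1) × 0.05 = 5.95.
- Unequal clusters, relative-efficiency form: L = 5/5.95 = 0.840, and 5.95 / [1 − 0.65² × L(1 − L)] = 5.95/0.943 = 6.31.
- Unequal clusters, CV form: 1 + [(0.65² + 1) × 100 − 1] × 0.05 = 8.06.

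**3. Standard error and real error rate.** Ignoring villages, SE = 2 × √(2/400) = 0.141. The real SE is larger by √DE, so the real type I error of a nominal 5% contrast of change is 2 × [1 − Φ(1.96/√DE)].

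| Reading | DE | √DE | Real SE | Real error |
|---|---|---|---|---|
| ICC 0.05, equal clusters | 5.95 | 2.44 | 0.345 | 42% |
| ICC 0.05, CV 0.65, relative-efficiency form | 6.31 | 2.51 | 0.355 | 44% |
| ICC 0.05, CV 0.65, CV form | 8.06 | 2.84 | 0.402 | 49% |
| ICC 0.01 (assumed), equal clusters | 1.99 | 1.41 | 0.199 | 16% |

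Effective sample size per arm at ICC 0.05 is 400/5.95 = 67 down to 400/8.06 = 50.

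**4. Simulation check** (three occasions, no true effect, 3000 runs per setting, ICC 0.05). The 24-month change contrast that ignores villages rejected in 43% of runs with equal clusters and 47% with CV 0.65. The three-occasion group-by-time F test rejected in 62% and 66%. A t test on the eight village means rejected in 4.7% to 5.7%.

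**5. If 0.05 is the ICC of single-visit scores.** The ICC of change is then 0.05(1 − c) / [0.05(1 − c) + 0.95(1 − r)], where c is the autocorrelation of village effects and r that of individuals. The article gives neither. Assuming r = 0.6 to 0.8:
- c = 1: change ICC 0, error 5%.
- c = 0.9: change ICC 0.013 to 0.026, error 20% to 30%.
- c = 0.5: change ICC 0.062 to 0.116, error 46% to 58%.

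**6. Within-arm reading.** The variance of a mean change within one arm is multiplied by the same design effect, so steps 2 and 3 apply to its standard error. The error rates in step 3 then concern a claim of change over time, not a claim of treatment effect.

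**The case against.** The strongest reply is that this is a supplementary analysis described in one condensed sentence. Most of that stands.

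- A reader might infer that the primary result is at risk. It is not: the 24-month outcome is assigned to the multilevel model with a village random effect, and nothing makes the ANOVA a deciding test.
- A reader might infer that the 12-month question rests on the ANOVA alone. The article says that secondary outcomes at other time points get similar methods, and cognition at 12 months is a secondary objective. That contrast is plausibly already covered by a multilevel model.
- A reader might state as fact that the ANOVA treats residents as independent. The article never says so, and a nested village factor is possible. What the text supports is that no village term is named, and that the clustering sentence is confined to the other models.
- A reader might add that anyone with a missed visit is dropped. The same section plans multiple imputation. It does not say that the imputed data feed the ANOVA, so the point is open.
- A reader might expect the ANOVA always to look more significant than the multilevel model. That is too certain: the multilevel model also adjusts for baseline and covariates, and the ANOVA is not said to.
- The 42% to 49% is conditional on the ICC being that of change and, above 42%, on the CV being that of cluster size. The first is supported by the calculation being about change but is not stated; the second is not stated either.

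What survives is narrower. A named test on the main outcomes, at the common 0.05 level, has no stated provision for the unit of randomisation. Nor is this merely detail left to a separate analysis plan: the article itself fixes the method and states the clustering provision only for the other models.

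**Conclusion.** The point holds for the supplementary time-course results only. Run in standard form, the ANOVA would understate the standard error about 2.4-fold at the plan's ICC of 0.05 with 100 per village, and a nominal 5% between-arm contrast of change would have a real error of about 42%. That rests on the ICC applying to change and on no village term being added. The inflation shrinks with a smaller ICC of change. It disappears if village effects are fully stable over time, which the article does not claim. Under the within-arm reading, the understated standard error remains and no randomised comparison is made.

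**What to change.** Replace the ANOVA with one linear mixed model of the 12- and 24-month scores:
- fixed effects for arm, visit, arm-by-visit and baseline score;
- random effects for village, and for village-by-visit if estimable;
- within-person correlation between visits;
- a small-sample degrees-of-freedom correction for eight clusters, such as Kenward-Roger or Satterthwaite.

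Take the 24-month contrast as primary and the 12-month contrast as secondary.

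Including county is optional. Eight villages less an intercept and arm leave 6 village-level degrees of freedom; three county terms reduce this to about 3. A test using 1.96 would then have roughly 14% error (the probability that |t| on 3 df exceeds 1.96), so the correction is essential if county is kept.

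Alternatively, keep the ANOVA and state that it is descriptive, without p-values. Either change alters analysis wording only and uses the same data.
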